**Fig. 4 Fig4:**
[figure not shown]
Test locations for perimetry. The same 21 locations will be used for 3 test paradigms, the Humphrey Field Analyzer (for photopic sensitivity) and two-color dark-adapted microperimetry (cyan 505 nm, red 627 nm) using the MAIA-S. Perimetry will be tested in one eye only (the eye undergoing testing for RMDA tested at 5° and 12°). Targets are 0.43° in diameter (Goldmann III). Locations were chosen to sample closely near the fovea, where cell densities change rapidly with eccentricity and an effect of Bruch’s membrane lipidization is expected. In addition, targets in perifoveal and paramacular locations are included where rod density is high and subretinal drusenoid deposit is expected

Since cone-mediated sensitivity in the visual field is optimized for photopic light conditions, we will also assess sensitivity using a Humphrey Field Analyzer with a full-threshold procedure for a test grid identical to that of the S-MAIA as indicated above. The same eye as tested for dark adaptation and S-MAIA testing will be used.

Best-corrected visual acuity and spatial contrast sensitivity will be measured under both photopic (100 cd/m^2^) and mesopic (0.1 cd/m^2^) conditions for each eye separately. Visual acuity will be assessed using the Electronic Visual Acuity (EVA) tester [89] (JAEB Center, Tampa FL) and expressed as logarithm_10_ of the minimum angle of resolution. To achieve background mesopic luminance, participants will view the EVA through a 2.0 log unit neutral density filter. The “low luminance deficit (LLD)” for acuity [62], as it is called, is defined as the decrease in logMAR that occurs under mesopic conditions as compared to acuity under photopic conditions. Analogous to measuring LLD for acuity, we will assess the LLD for contrast sensitivity by measuring contrast sensitivity under both photopic and mesopic conditions as described above, using the Mars chart [90] (Mars Perceptrix, Chappaqua NY). The LLD for contrast sensitivity will be expressed as the difference in logarithm_10_ of sensitivity under photopic versus mesopic conditions. Both the EVA visual acuity tester and the Mars contrast sensitivity chart have high test-retest reproducibility [89, 91].

With respect to multi-modal imaging, protocol elements consist of color fundus photography (CFP), SDOCT, near-infrared (NIR) reflectance, OCT angiography, and quantitative autofluorescence (qAF). OCT angiography is captured on the study eye only (eye tested for RMDA). Other modalities are captured on both eyes. CFP is used to document eligibility and AMD status. After pupil dilation, 3-field (30° diameter) stereo-fundus, digital photographs using a FF450^+^ camera (Carl Zeiss Meditec, Dublin CA) are taken. Photos will be evaluated by a trained grader with established inter-grader agreement (κ = 0.84) for presence and severity of AMD using the AREDS 9-step classification system [69]. The AREDS system grading is also converted to the more recently developed Beckman system [92]. Inter-grader agreement will be periodically monitored using a second grader with disagreements adjudicated by a fellowship-trained retina specialist ([name]). In addition, with the FF450+ camera, CFPs are captured at 2 additional magnifications (20° and 50°).

We acquire spectral-domain OCT volumes (Spectralis HRA + OCT, Heidelberg Engineering, Heidelberg, Germany; λ = 870 nm; scan depth, 1.9 mm; axial resolution, 3.5 μm per pixel in tissue; lateral resolution, 14 μm per pixel in tissue), with Automatic Real-Time averaging > 9, and quality (signal-to-noise) 20–47 dB. B-scans (*n* = 121 scans, spacing =60 μm) are horizontally oriented and centered over the fovea in a 30°× 25° (8.6 × 7.2 mm) area. To permit averaged OCT-angiography scans of the choriocapillaris [93], we take two volumes for OCT-angiography centered at each of two locations in the study eye, the fovea and the 5° RMDA test location. Both of these cover 15°× 15° (4.3 × 4.3 mm, *n* = 384 scans, spacing = 11 μm). To detect SDD, which extend not only beyond typical SDOCT volumes but also outside the vascular arcades and nasal to the optic nerve head [94, 95], we use 50° *en face* fundus imaging with CFP (Zeiss FF450+), NIR-reflectance, and qAF (λ_ex_ = 488 nm), in both eyes. Quantitative AF technology includes an internal reference in the light path and allows valid comparison of RPE-attributed signal between baseline and follow-up and across patients [96]. Prior to capturing qAF images in 30° macular fields of both eyes we will bleach the retina, as recommended. On an exploratory basis for utility in fundus grading, we will take 50° posterior pole images with a white-light confocal device (Eidon, Centervue, Fremont, CA) for enhanced fundus detail in a 14.8 MB file format.

In terms of laboratory measures, plasma C-reactive protein (CRP), an acute-phase responder and sensitive indicator of systemic inflammation, will be quantified in an automated analyzer using turbidimetric reagent. Elevated CRP is associated with AMD, increases progression risk [97–99], and associates with delayed RMDA in persons with normal maculas [100]. Human choroid is immunoreactive for monomeric CRP [101–104], likely derived from circulating pentameric CRP (of hepatic origin) following irreversible dissociation after binding to damaged cells. CRP may be an effect modifier in associations between retinal structure and RMDA and scotopic sensitivity. DNA will be extracted to examine associations for *ARMS2* and *CFH* with visual function and retinal structure. We will examine the specificity of our recent finding that *ARMS2* and *CFH* are associated with delayed RMDA [17], using techniques previously described [17], by testing for associations with other types of scotopic and photopic dysfunction. Because visual tasks assess precise retinal mechanisms, the specificity of this relationship can potentially inform about the function of these high-risk alleles. For reasons elaborated in the Future Directions, we will also measure serum high-density lipoprotein (HDL) levels by standard enzymatic colorimetry assays and risk alleles for HDL genes associated with AMD risk and possibly involving systemic and intraocular mechanisms in lipid transfer [34].

Questionnaires are used to collect self-report information through interviewer-administration. Demographic information on birthdate, gender, race/ethnicity, education completed, and marital status is collected. General health information is collected by a questionnaire asking about the presence versus absence of 15 chronic medical conditions in the form of “Has a doctor ever told you that you have. ..? ” [100]. Participants are asked to bring a list of current prescription medications, over-the-counter medications, and nutritional supplements to their initial visit; these items are then inventoried by the coordinator. Questionnaires are also administered addressing alcohol use and smoking [100]. The Low Luminance Questionnaire (LLQ) [105] asks about difficulties that participants have in performing the visual activities of daily living under lower luminance or dim illumination conditions, including adapting to darkness and bright lights. Responses are organized into six subscales including driving, extreme lighting, mobility, emotional distress, general dim lighting and peripheral vision. The Vision Impairment in Low Luminance (VILL) questionnaire is also administered, which has content similar to that of the LLQ, focusing on visual difficulties under challenging lighting conditions. It is being used in the MACUSTAR study [106], an observational study on AMD being performed in Europe. We will examine the relationship between the VILL and LLQ in the ALSTAR2 sample. A cognitive screening test will be administered to obtain information on general cognitive status. The Montreal Cognitive Assessment (MOCA) [107] has been selected as a cognitive screener; it is designed for detection of mild cognitive dysfunction, possibly present in older adults recruited through eye clinics.

### Sample size determination and analysis plan

Each study aim will estimate the association between two continuous variables, visual function and structure (e.g., RMDA as measured by rod-intercept time and RPE thickness). Sample size requirements are based upon the calculation of correlation coefficients. Table 3 presents sample sizes required to have at least 80% power (alpha = 0.05) to detect a range of correlation coefficients as statistically significant. Because no published study uses specifically our proposed structure and function measures and our patient population, we used the literature reporting structure-function correlations ranging from 0.1–0.6 in aging and AMD to guide sample size estimation [86, 108–111]. Studies finding correlations > 0.3 typically address later stages of AMD (intermediate AMD and GA). Because we focus on early disease, we anticipate weaker structure-function relationships, ~ *r* = 0.2. Using these considerations as guides to compute sample size, 193 AMD and 193 normal patients are required in order to achieve statistical power of 80%. Given the longitudinal study design, we bolster this sample size for losses to follow-up over 3 years and the inability of some patients to perform some vision tests. Based on the ALSTAR1 experience [16, 71], we increase sample size by ~ 20% to address anticipated loss to follow-up. Thus, we enroll 240 each of persons in normal macula health and those with early AMD. We will also be including study of 20 young adults ages 20 to 30 years old to serve as a reference group, against which the older adults can be compared. They will participate in the same baseline protocol as the older adults.

**Table 3 Tab3:** Sample Size Determination in ALSTAR2

Pearson correlation coefficient for alternative hypothesis	Sample size required
0.2	193
0.3	84
0.4	46

Statistical analyses will be conducted using SAS v. 9.4 (SAS Institute, Cary, NC) using a 2-sided alpha of 0.05. Although scientifically distinct, the 3 aims require similar analytical techniques, reflecting the underlying data structure being collected. A longitudinal study means that all primary measures will be collected at two points in time. However, for many measures, data will also be collected at specific retinal locations. Thus, statistical comparisons between structural and functional measurements must account for repeated measures and clustering of measurements within participants, i.e., eyes. The primary statistical tool to test hypotheses will be a mixed effects model. These models will be used to test both cross-sectional associations as well as prospective associations on changes in structure and function, both of which have hierarchical effects that need to be taken into account. The primary distinction between the models for cross-sectional and prospective associations is the inclusion of a time parameter in the latter. Prospective models will be used to explore the associations between joint changes in structural and functional measures but also whether baseline structural measures can predict functional changes. For example, considering the primary hypothesis for Aim 2A, i.e., RPE thickness is associated with scotopic dysfunction, the dependent variable will be RMDA and the main independent variables will be RPE volume (area x thickness across the macula) and mean normalized reflectivity. These measurements will be explored for their independent and joint effects on RMDA using unadjusted and adjusted models. For the cross-sectional analysis, the model will need to consider only the clustering of measurements within participants (i.e., at different locations). For the prospective analysis, a term must be added to the model to account for baseline and follow-up measurements.

It is important to note that the structure of secondary dependent variables (e.g., visual acuity) is heterogeneous with respect to clustering. For example, worse and better eye visual acuity is analyzed at the person level and therefore with person level independent variables, there is no need to account for clustering in the cross-sectional analyses; the prospective analyses will be akin to a repeated measures ANOVA model. The aforementioned analyses will all involve assessment of the confounding and/or modifying effects of demographic characteristics (e.g., age), behavioral characteristics (e.g., smoking) and biological measurements (e.g., CRP). It is important to note that the dearth of prior literature on structure-function relationships makes it difficult to a priori determine which measures may serve as confounders and/or effect modifiers. Further, the existing literature almost never takes these variables into account. However, based upon the extensive literature on risk factors for AMD incidence and progression, it is not unreasonable to consider characteristics such as smoking, chronic medical conditions, among others, as playing a role in these associations. Other variables such as age and whether eyes have progressed in AMD severity on the AREDS 9-step system will be addressed as confounder/effect modifier candidate variables. We will use multivariable analyses to evaluate the independent effects of the structural variables on slowed RMDA and other visual functions. These analyses will allow us to evaluate the relative extent to which each of the structural variables contribute to scotopic dysfunction. We will utilize standard techniques to evaluate the confounding and/or modifying effect of demographic and behavioral characteristics, seeking to identify structure-function relationships that are independent.

We will examine the relationship between self-reported vision problems (e.g., Low Luminance Questionnaire results) and structural and functional variables. These analyses will be structured the same as those described for the primary hypotheses. We will explore cross-sectional relationships as well as whether structural-functional changes over time are reflected in self-report measures. Although self-report measures are at the person-level, many of the structure-function measures, as described above, are clustered, thus for the simplest cross-sectional analyses, ANOVA will be used. For more complex cross-sectional and prospective analyses, mixed models will be employed.

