In AMD, the presence of extracellular deposits in the macula – soft drusen and subretinal drusen deposits (SDD, a.k.a reticular pseudodrusen) – increase AMD progression risk and compromise metabolic exchange between the ChC and outer retinal cells. Our hypothesis is that scotopic dysfunction will be accentuated where drusen and/or SDD are present, with SDD having a greater negative impact than drusen on scotopic function both cross-sectionally and prospectively.RPE cell bodies lose epithelioid morphology before anterior migration or apoptosis, as evidenced by variability and thickening of the RPE band in OCT and dimming of fundus autofluorescence signal from organelles believed to contain bis-retinoids. The thickness of photoreceptor- and RPE-attributable reflective bands will be assessed for context. Our hypothesis is that variability in RPE cell bodies is associated more strongly with scotopic dysfunction than photopic function both cross-sectionally and prospectively.The vascular density of the ChC (proportion of BrM covered) is a measure of direct metabolic exchange capacity between plasma and outer retinal cells in aging and early AMD. ChC vascular density declines in aging, under individual drusen, and in complete RPE and outer retinal atrophy (cRORA; geographic atrophy) [21]. Our hypothesis is that decreased ChC vascular density is more strongly associated with scotopic dysfunction than photopic function both cross-sectionally and prospectively.

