**Fig. 5 Fig5:**
[figure not shown]
Center-surround model of cone resilience and rod vulnerability in aging and AMD. In the top row is an en face view of help via xanthophyll carotenoid pigment (orange) and harm via soft drusen/ basal linear deposit, as shown in Fig. 1. In the bottom row help and harm are plotted on one vertical axis, positive and negative directions, respectively. **a**. The distribution of xanthophyll carotenoids, as shown in Fig. 1, is a focused center of help in the central macula. **b** The distribution of soft druse material is shown as a broad circular area of harm (see Fig. 1). **c** Together, help and harm make a center of foveal cone resilience on top of a surround of para- and perifoveal rod vulnerability. The resemblance of this map to the maps of photoreceptor loss in human retinal aging in Fig. 1 are striking. See text for further details. Figure prepared with assistance of [name] MS.

Longitudinal population-based studies have shown that drusen conferring risk for progression to late AMD are remarkably concentrated in the central macula [42–44, 117]. Drusen prevalence decreases by 2/3 from the central subfield of the ETDRS grid to the inner ring [42–44, 117], suggesting a basis in the biology of healthy fovea and raising four noteworthy points. First, it is interesting that cones are also highly concentrated in the central subfield and decrease in density by 2/3 in the inner ETDRS ring (Table 1). Second, Müller glia are concentrated in the foveal center and may equal cones in number [118, 119]. Third, the foveal center is rich in xanthophyll carotenoid pigments (lutein, zeaxanthin, meso-zeaxanthin) [120, 121], which could serve to protect the fovea. Fourth, Müller glia are newly indicated as major xanthophyll reservoirs by research on other glio-degenerative retinal diseases [121–126]. Thus, protection of foveal cones in aging and AMD can be in part attributed to the activity of Müller glia, a cell type frequently overlooked in AMD pathogenesis. The Center-Surround model (Fig. 5a) includes a sharp peak of protection due to xanthophyll carotenoids localized to foveal cones and Müller glia.

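### Pooled location-level models that handle only clustering leave the Aim 1 drusen and SDD effects confounded by normal retinal topography

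*Protocol article*

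**What the plan says.** The section Sample size determination and analysis plan makes a mixed effects model the main tool, says the three aims need similar techniques, and works through Aim 2A. There the outcome is RMDA and the exposures are RPE volume over the macula and mean normalized reflectivity. It then states: "For the cross-sectional analysis, the model will need to consider only the clustering of measurements within participants (i.e., at different locations". The next sentence adds a baseline/follow-up term for the prospective version.

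Candidate confounders and modifiers are "demographic characteristics (e.g., age), behavioral characteristics (e.g., smoking) and biological measurements (e.g., CRP", plus chronic conditions and whether an eye has progressed on the AREDS scale.

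Aim 1 (specific aims, Background) is a claim about places in the retina: "scotopic dysfunction will be accentuated where drusen and/or SDD are present, with SDD having a greater negative impact than drusen".

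Elsewhere the article describes how the retina varies by place:
- Table 1 gives older-adult rod density as 15,016 (centre), 56,105 (inner ring) and 96,265 (outer ring) per mm².
- The Fig. 4 legend says "targets in perifoveal and paramacular locations are included where rod density is high and subretinal drusenoid deposit is expected".
- The Discussion says "Drusen prevalence decreases by 2/3 from the central subfield of the ETDRS grid to the inner ring".

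**The concern.** A participant effect corrects standard errors for repeated measurements in one eye. It does not remove a difference in mean sensitivity between places. Age, smoking, CRP and AREDS progression are all constant across the test points of one eye, so they cannot remove it either.

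If normal sensitivity follows rod density, points that carry drusen are on average less sensitive, and points that carry SDD more sensitive, before any deposit does harm. A pooled model without location compares deposit points with all other points in the macula. Aim 1 asks whether function is worse than expected for that place. At stake are the separate drusen and SDD effects and, most of all, the comparison between them, because the two biases have opposite signs.

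**Working it through.** **The plan's own figure.** The inputs are "sample sizes required to have at least 80% power (alpha = 0.05"), "using a 2-sided alpha of 0.05" and r = 0.2 ("we anticipate weaker structure-function relationships"). Fisher z gives n = ((1.960 + 0.842)/atanh 0.2)² + 3 = 193.97. With the small-sample correction r/(2(n − 1)) it gives exactly 193. Allowing for 20% loss, 193/0.8 = 241, against 240 enrolled per group. The sample size stands. It concerns a single correlation and does not address location.

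**Gradient in the documents.** 96,265/15,016 = 6.4-fold from centre to outer ring, or 0.81 log10 units. Inner to outer ring is 0.23 log10 units. From 5° to 12° superior, 116,683/62,043 is 0.27 log10 units.

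**Assumptions (not in the documents).** Normal sensitivity rises k dB per log10 rod density. There are 240 participants and 21 points (the Fig. 4 count; the microperimetry text says 23), placed 1/4/8/8 in four bands with densities 15,016 / 56,105 / 96,265 / 116,683. Drusen prevalence by band is 60/20/8/3% (the first step matches the stated two-thirds fall) and SDD prevalence 2/5/12/15%. Between- and within-person SDs are 2 dB each.

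**Hand check at k = 10.** Relative to the centre, normal sensitivity by band is 0, 5.72, 8.07 and 8.90 dB.
- Expected drusen points per eye: 0.60, 0.80, 0.64, 0.24 (sum 2.28). Mean normal sensitivity at them is 11.88/2.28 = 5.21; elsewhere it is 146.76/18.72 = 7.84. Spurious difference −2.63 dB.
- Expected SDD points: 0.02, 0.20, 0.96, 1.20 (sum 2.38). Mean 19.57/2.38 = 8.22; elsewhere 139.07/18.62 = 7.47. Spurious difference +0.75 dB.

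Both scale in proportion to k.

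**Simulation with no true deposit effect** (random-intercept model, 300 replicates per row, no location term; each cell gives rejection rate and bias):

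| k | Drusen, all points | SDD, all points | Drusen, centre dropped | SDD, centre dropped |
|---|---|---|---|---|
| 0 | 6%, 0 dB | 5%, 0 dB | 6%, 0 dB | 5%, 0 dB |
| 1 | 87%, −0.28 | 8%, +0.06 | 16%, −0.09 | 8%, +0.04 |
| 2 | 100%, −0.54 | 33%, +0.14 | 45%, −0.20 | 14%, +0.08 |
| 5 | 100%, −1.35 | 92%, +0.33 | 99%, −0.48 | 54%, +0.20 |
| 10 | 100%, −2.70 | 100%, +0.66 | 100%, −0.98 | 97%, +0.41 |

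With band fixed effects, rejection is 3 to 6% and bias about zero in every row.

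A second set of assumptions used 193 participants, 23 points placed 3/8/12, drusen 30/10/5%, SDD 2/5/10% and k from 2.5 to 10. It gave 100% for drusen and 57 to 100% for SDD. With central points dropped it gave 12 to 88% and 16 to 82%. With location effects it gave 3 to 7%.

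**Ranking, with true effects of drusen −1 dB and SDD −2 dB.** Under the first set with all points, estimates without location are −1.54 and −1.87 at k = 2 (order kept), −2.35 and −1.67 at k = 5 (reversed), and −3.71 and −1.35 at k = 10 (reversed). With the centre dropped the order is kept at k = 5 (−1.50 and −1.81) and reverses only at k = 10 (−1.97 and −1.60). Under the second set the average order reverses at k = 5 and 10 with central points, and not without them. With band effects the estimates are −1.0 and −2.0 throughout.

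**The plan's own example.** With a macula-wide exposure, RMDA at 5° and 12°, and an assumed 3-minute difference between the spots, rejection is 5.0% with or without a location term (3,000 replicates). If structure is instead measured at each spot, and both structure and rod-intercept time differ by 0.3 to 1.0 SD between spots (assumed), rejection is 14 to 100%.

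**The case against.** The strongest reply is context. The sentence closes the Aim 2A example, whose main exposure is summed over the macula, and the calculation confirms that topography does no harm there. The word *only* mainly contrasts with the time term of the prospective model. The covariate list is open-ended, and the article condenses a fuller plan. It also plans topographic examination, sensitivity outcomes by eccentricity and meridian, and a within-subject comparison of the 5° and 12° RMDA tests. An analysis confined to one eccentricity escapes this bias. Thresholds that are not rod-mediated are excluded from scotopic sensitivity, which removes part of the central gradient.

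Most of this stands as a limit on the point. A reader might infer that the plan treats locations as exchangeable, or admits only person-level covariates. Neither is supported: no covariance structure is stated, the list gives examples, and AREDS progression is an eye-level variable.

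What does not stand is that the plan already deals with the matter. The topographic statements describe outcomes and intentions, and none puts location into the stated test. The plan extends similar techniques to all three aims, so the clustering-only description is the only one given for Aim 1.

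**Conclusion.** The point holds for models that pool test locations and use a location-specific exposure, chiefly the Aim 1 drusen and SDD effects and their comparison. The direction follows from the article's own topography, provided normal scotopic sensitivity rises with rod density: drusen look more harmful and SDD less harmful, against the hypothesised ranking.

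The size is not fixed by the documents. It rests on the assumed gradient, prevalences, point layout and SDs, and on deposits coded as present or absent. False rejection runs from nominal (no gradient) to 100%, is generally lower for SDD, and falls when central points are excluded.

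A reader might infer that normal topography by itself must produce significant results, or must reverse the ranking. The documents do not support either as an unconditional claim. Reversal needs the steeper assumed gradients and, in nearly every scenario tried, the central points as well; the one exception is the steepest gradient under one set of assumptions. Macula-wide exposures are unaffected.

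**What to change.** In Sample size determination and analysis plan, limit the clustering-only statement to exposures that do not vary by location. For pooled models with location-specific structure (two-color microperimetry, the Humphrey grid, and RMDA at 5° and 12° with local structure), add a fixed effect for test location or eccentricity alongside the participant effect. An alternative is to analyse deviations from the normal group's mean at each location. This is not equivalent, because the reference differs and estimating it adds error. Base the drusen and SDD conclusions on the adjusted coefficients.

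Analyses within one eccentricity, person-level exposures and the separate Center-Surround topography work need not change.

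The cost is wording and, with 21 locations, 20 degrees of freedom out of about 193 × 21 = 4,053 observations in one group. No new data or participants are needed. Some precision is lost for deposits found almost only at one location.

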## Methods/design

### Study design

The study was approved by the Institutional Review Board of the University of Alabama at Birmingham (UAB). All enrollees will provide written informed consent after the nature and purpose of the study are explained. Conduct of the study follows the tenets of the Declaration of Helsinki.

ALSTAR2 is a prospective cohort study with baseline measurements that are repeated at follow-up 3 years later. At baseline two groups of adults ≥60 years old are enrolled whose AMD status is determined by the AREDS 9-step classification system for color fundus photographs [69, 70]: (1) Those in normal macular health (AREDS grade 1) in both eyes, i.e., drusen equivalent diameter < 125 μm without increased pigmentation or depigmentation/ GA. (2) Those having early AMD (AREDS grade 2–4) in at least one eye, i.e. different combinations of drusen abundance and pigmentary change [69, 71]. The fellow eye can be any AREDS grade. We selected a 3-year follow-up period since changes in structural and functional characteristics in aging and early AMD are detectable over this period [16, 18, 19, 72]. We chose to use the AREDS 9-step grading system, despite the limitations of color fundus photography in revealing important details of AMD pathology, because it is validated and widely used [73, 74], and an equivalent system for OCT or other technology is yet to be devised. However, key pathology like SDD is visible in good color fundus photographs [75, 76] and are amenable to deep learning approaches [77] for detection and staging.

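### AREDS progression, known only at year 3, is named a candidate confounder, but it cannot confound the models asking whether baseline structure predicts functional change

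*Protocol article*

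**What the plan says.** All places are in the protocol article.

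- **Role given to progression** (Sample size determination and analysis plan): next to age, "whether eyes have progressed in AMD severity on the AREDS 9-step system will be addressed as confounder/effect modifier candidate variables".
- **Prospective question** (same section): the models explore joint changes in structure and function, and also "whether baseline structural measures can predict functional changes". The Aim 2A example there is run both unadjusted and adjusted.
- **Purpose of adjustment** (same section): the multivariable work is described as "seeking to identify structure-function relationships that are independent".
- **What the grade measures** (Study design): early AMD, AREDS grades 2–4, is described as "different combinations of drusen abundance and pigmentary change". Measurements are taken at baseline and again 3 years later.
- **Planning basis** (Sample size determination and analysis plan): tests are made "using a 2-sided alpha of 0.05". For early disease, "we anticipate weaker structure-function relationships", put at about r = 0.2, which gives 193 per group for 80% power.

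**The concern.** A confounder of the link between baseline structure and later functional change must not itself result from the exposure. Progression between baseline and year 3 comes after baseline structure, and the article's own biology makes it a consequence of that structure. Conditioning on it changes the question from whether structure predicts functional decline to whether it does so apart from any graded progression. If part of the true effect runs through progression, a useful structural predictor looks weaker. If other causes of functional decline also drive progression, conditioning on it links those causes to structure and adds bias.

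The article wants structural markers that are valid against function, so the adjusted estimates of independent effects will carry weight. An analysis plan written from this text would inherit the role it assigns.

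**Working it through.** **1. The plan's own figure.** Inputs: two-sided alpha 0.05, power 80%, r = 0.20. With Fisher's z,

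N = ((1.960 + 0.842) / atanh(0.20))² + 3 = (2.802 / 0.2027)² + 3 = 193.97.

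Table 3 states 193. For r = 0.3 and 0.4 the formula gives 84.9 and 46.7, against 84 and 46 stated. The planning figures reproduce. At n = 193, power for r = 0.20 is 79.8%.

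**2. Where progression sits, on the article's own statements.**

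- *Timing.* With visits only at baseline and 3 years, progression is fixed at the same visit as the functional change.
- *Aim 1.* Drusen and subretinal drusenoid deposits are the exposures in the specific aims, and AREDS grades are built from drusen and pigment. Progression is therefore partly change in the exposure.
- *Aim 3.* The section on physiology and aging says that a lipid barrier in Bruch's membrane and choriocapillaris decline together produce soft drusen and their growth. Progression is a plausible intermediate.
- *Aim 2.* For the retinal pigment epithelium (RPE) the same role is plausible but less direct.
- *From function to progression.* The Background reports delayed RMDA as a risk factor for incident early AMD. Progression may thus be a common effect of structure and function.

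**3. Illustration of size.** The documents give neither a progression rate nor a mediated share, so these inputs are assumptions: a fraction p of eyes progress (20% or 25%), baseline structure X correlates a = 0.3 to 0.7 with latent severity, and the total r is about 0.20. Progression M marks the top p of latent severity. Then

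- r_XM = a·k, with k = φ(z_p)/√(p(1−p)), which is 0.70 at 20% and 0.73 at 25%
- partial r = (r_XY − r_XM·r_MY) / √((1 − r_XM²)(1 − r_MY²))
- power = Φ(√(193 − 4)·atanh(partial r) − 1.96)

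*Half mediated, through latent severity* (p = 20%, a = 0.5). Direct part 0.10; severity coefficient 0.10/0.5 = 0.20. Correlation of severity with function: 0.10 × 0.5 + 0.20 = 0.25. So r_MY = 0.70 × 0.25 = 0.175 and r_XM = 0.35. Partial r = (0.20 − 0.061)/0.922 = 0.150. Power = Φ(13.75 × 0.152 − 1.96) = Φ(0.12), about 55%.

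*Half mediated, through the indicator itself* (p = 25%, a = 0.7). r_XM = 0.514; r_MY = 0.10 × 0.514 + 0.10/0.514 = 0.246. Partial r = (0.20 − 0.126)/0.832 = 0.088. Power = Φ(13.75 × 0.089 − 1.96) = Φ(−0.74), about 23%. A simulation of this kind of setting (n = 193, 25% progressing, total effect 0.211) moved the estimate to 0.101 and power from 81% to 24%. With a = 0.3, r_XM = 0.22, r_MY = 0.48, partial r is 0.11 and power about 33%.

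| Assumed share mediated, and route | Partial r after adjustment | Power at n = 193 |
|---|---|---|
| None | 0.18–0.20 | 68–78% |
| Half, through latent severity | 0.15–0.16 | 53–59% |
| Half, through the indicator | 0.09–0.11 | about 24–33% |
| All, through latent severity | 0.11–0.12 | 35–38% |
| All, through the indicator | about 0 | about 5% |

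The 59% comes from runs with 25% progressing and a total effect of 0.21.

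**4. Collider bias.** Adding an assumed unmeasured cause of both progression and functional loss, a half-mediated effect went from 0.200 to 0.068 (power 72% to 13%), and a fully mediated one from 0.166 to −0.034. The strength of such a cause is not in the documents, so these runs show direction only.

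**The case against.** The strongest reply is that the article commits to nothing. Progression is a candidate, effect modification is offered as an alternative role, the article says confounders are hard to name in advance, and the Aim 2A example keeps unadjusted models. All of this stands. A reader might infer that the plan will adjust for progression and so remove the effect it seeks; the text supports only that it may do so and that this can weaken the effect. The effect-modifier role does not escape the difficulty, because it too conditions on something that happens after baseline.

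A reader might also infer that the usual confounder-selection methods are bound to pick progression. The documents do not support that. The sentence on those methods concerns demographic and behavioral characteristics and names no method.

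Third, for Aims 2 and 3 one may fairly ask whether change in RPE or choriocapillaris tracks function beyond what color photographs grade, given the limits of color photography that the article acknowledges. That also stands: in joint-change models, conditioning on progression targets a different estimand and is not plainly an error. The description of progression as part of the exposure fits Aim 1 only.

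Finally, the size depends on assumptions. With the effect running through latent severity, no scenario tried without an unmeasured common cause removed it entirely. Disappearance of the effect needed full mediation through the indicator; the sign reversal in step 4 needed full mediation plus an unmeasured common cause.

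Detail left to a fuller analysis plan would be no fault. Here, though, the article itself assigns a role, and for one stated question that role is wrong.

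**Conclusion.** The point holds for the prospective models of baseline structure predicting functional change. Progression during follow-up cannot confound that association, and adjusting for it can attenuate the association or add collider bias. Unadjusted and cross-sectional models are not affected.

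The documents do not determine the size. Under the assumptions of 20–25% progressing and half of an effect of about 0.20–0.21 mediated, power falls from about 80% to between about 24% and 59%. If nothing is mediated, and there is no common cause, the loss is small (68–78%). Certainty is high on the logic and low on the magnitude. The stronger claim, that the plan removes the effect it is looking for, is not supported.

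**What to change.** In the analysis plan:

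- Remove AREDS progression from the confounder candidates for models in which baseline structure predicts functional change. Adjust these only for baseline covariates, such as age.
- Use baseline AREDS grade only where it is neither part of the exposure nor downstream of it: not by default in Aim 1, where it overlaps drusen; with care in Aim 3, where it may follow from choriocapillaris decline; and only where it varies. In the normal group it is grade 1 in both eyes by definition.
- Keep progression as an outcome, or in a secondary mediation or stratified analysis labelled descriptive, since stratifying on it still conditions on a post-baseline variable.
- In joint-change models for Aims 2 and 3, label any conditioning on progression as a separate estimand: association beyond fundus-graded progression.

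The core change is one sentence, with short labels for the secondary analyses. No new data are needed and the sample size does not change.
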